#### Statistical power

Statistical power for the primary hypotheses is simulated using model (3) with *β*_1_ = *β*_12_ = 0 and dropping *g*_1_(*t*;ψ) from the model. It is based on a planned constant sample size (denominator) of *N* = 200 patients/practice at each time point. For the communication outcome, we assumed *β*_0_ = 1.4 corresponding to a baseline rate of 80 % for a low ready practice (*X*_i2_ = 0). For the shared decision-making outcome, we set *β*_0_ = −0.8 giving 30 % baseline when *X*_i2_ = 0. Finally, we fixed *β*_2_ = 0.05 and *β*_3_ = 0.05, variances *σ*_0_^2^ = 0.42 and *σ*_1_^2^ = 0.32, and covariance *σ*_01_ = −0.15. These values for variance components are adopted from Aim 1 for lack of preliminary data for Aim 2. They are considered reasonable estimates because the statistical analysis for Aim 2 involves a random effects logistic regression model for repeated binomial data. Power exceeds 98 % for detecting differences as small as 0.04 in proportions between intervention and control (see Additional file 2).

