#### Statistical power

Power to detect the effect of intervention after 12 months with respect to the outcome of hypertension control is simulated for the stepped-wedge study design assuming 300 practices, and an average of *μ* = 1200 or 1600 patients per practice (assuming a typical practice has 4 physicians with 300 or 400 patients per physician). For data collection months *t* = s_i_ (baseline), *s*_i_ + 3, *s*_i_ + 6, *s*_i_ +9, *s*_i_ + 12, and *s*_i_ + 18 (6 months post-intervention follow-up), power calculations are based on practice-month summaries consisting of 1800 binomial observations (6 × 300). Power is determined by simulating data from a model similar to model (1) but, for simplicity, assuming no temporal trend:2$$ \mathrm{logit}\left\{E\left({Y}_{\mathrm{i}\mathrm{t}}/{N}_{\mathrm{i}\mathrm{t}}\Big|{b}_{\mathrm{i}0},{b}_{\mathrm{i}1}\right)\right\} = {\beta}_0 + {b}_{\mathrm{i}0} + {\beta}_2{X}_{\mathrm{i}2} + {\beta}_3{X}_{\mathrm{i}\mathrm{t}3} + {b}_{\mathrm{i}1}t $$where *X*_it3_ = 0 if *t* = s_i_; *X*_it3_ = (*t* – s_i_)/12 for *s*_i_ < *t* ≤ *s*_i_ + 12, and *X*_it3_ = 1 for *t* = *s*_i_ + 18. This model assumes a linear logistic trend during the active intervention period and a constant slope during the maintenance period equal to the 12-month intervention effect. Additionally, model (2) specifies a practice-specific intercept and slope assumed to be normally distributed with means 0 and variances *σ*_0_^2^ = 0.42, *σ*_1_^2^ = 0.32 and covariance *σ*_01_ = −0.15, values estimated from preliminary pretest-posttest data on 19 medical practices (not shown). Primary interest is in exp(*β*_3_), the practice-specific odds ratio of having a positive outcome (e.g., blood pressure controlled) after 12 months intervention relative to baseline. The number of patients in the i-th practice assumed to be constant across time (*N*_i_ = *N*_it_ for all *t*) was randomly selected from *N*_i_ ~ *N*(*μ*, *μ*^7/4^) to account for expected variability in practice size. A complete data set is then generated using model (2) with (*β*_0_ = 0.50, *β*_2_ = 0.05, *β*_3_ = 0.05) corresponding to a baseline of 62 % blood pressure control for least ready practices. The fraction of times that *H*_0_: *β*_3_ = 0 is rejected with two-sided *α* = 0.05 Wald tests under the correctly specified model was taken to be the simulated power for detecting a non-null odds ratio *β*_3_. When the true *β*_3_ = 0, the results represent simulated type I error, which is seen to be close to the nominal 0.05 significance level. The stepped-wedge design has excellent power for the outcome, percentage of hypertensive patients with controlled blood pressure (see Additional file 1).

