### Statistical analysis

For the primary hypotheses, communication and shared decision-making are binomial outcomes derived from patient surveys administered at baseline (*t* = s_i_) and at the end of the intervention period (*t* = s_i_ + 12). The model to assess improvement in these outcomes is a simplification of model (1) because there are only two repeated outcomes:3$$ \mathrm{Logit}\left({\uppi}_{\mathrm{i}\mathrm{t}}\right) = {\beta}_0 + {b}_{\mathrm{i}0} + {\beta}_1{X}_{\mathrm{i}1} + {\beta}_2{X}_{\mathrm{i}2} + {\beta}_{12}{X}_{\mathrm{i}1}{X}_{\mathrm{i}2} + {g}_1\left({t}^{*};\uppsi \right) + {b}_{\mathrm{i}1}t + {\beta}_3{X}_{\mathrm{i}\mathrm{t}3} $$where *X*_it3_ = 1 if *t* = s_i_ + 12 (end-of-intervention period) and *X*_it3_ = 0 if *t* = s_i_ (baseline). Note that exp(*β*_3_) is the odds ratio of a positive response (e.g., always communicated well, involved them in shared decision-making a lot of the time) after 12 months of intervention relative to the odds of a positive response at baseline, controlling for secular trends via ψ. The average causal effect of 12 months of intervention versus the control condition will be calculated as the average difference in proportions as described for Aim 1.

For the secondary hypothesis, model (2) will apply to claims data for the percentage of patients (a) hospitalized for a cardiovascular disease-related condition and (b) hospitalized for a CVD-related condition or died. For these outcomes, *X*_it3_ = 1 if *t* = s_i_ + 18 (6 months post-intervention) and *X*_it3_ = 0 if *t* = s_i_ (baseline). To assess whether primary care practice support decreases race-based disparities in these outcomes, the binomial data will be obtained for each race and practice and time point. Other facility-level patient outcomes are given in Table 4. Model (3) will be fitted to all binomial outcomes (e. g., percentage of patients…) using SAS Proc GLIMMIX. For continuous outcomes (e.g., a 10-year CVD Risk), an identity link function leading to a linear model fitted with SAS PROC MIXED will be used with variance weight 1/*N*_it_ where *N*_it_ is the observed number of patients in the *i*-th practice at the *t*-th month.

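### Aim 2 power: the listed effect (β3 = 0.05) is not the 0.04 difference claimed, and the figure above 98% holds only without the secular trend that model (3) keeps

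*Protocol article*

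**What the plan says.** The Statistical power section under Aim 2 simulates from model (3) with the region terms set to zero and g1 dropped. Its settings are:

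- Communication: β0 = 1.4, "corresponding to a baseline rate of 80 % for a low ready practice".
- Shared decision-making: β0 = −0.8, "giving 30 % baseline when" the readiness indicator is zero.
- Effects: "we fixed *β*_2_ = 0.05 and *β*_3_ = 0.05".
- Survey size: "It is based on a planned constant sample size (denominator) of" 200 patients per practice at each time point.
- Variance components: σ0² = 0.42, σ1² = 0.32, σ01 = −0.15. "These values for variance components are adopted from Aim 1 for lack of preliminary data for Aim 2".

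It then states power above 98% "for detecting differences as small as 0.04 in proportions between intervention and control" and refers to Additional file 2, which is not at hand.

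The Statistical analysis section for Aim 2 says that exp(β3) "is the odds ratio of a positive response" after 12 months relative to baseline. The model fitted there retains g1, and the odds ratio is described as controlled for secular trends.

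**The concern.** The paragraph gives one effect size on the logit scale and a different one on the proportion scale, and does not connect them. A reader who enters the listed settings obtains power near 29%, not above 98%, and cannot tell whether the planning effect is about 1 point or 4 points.

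Separately, the power model and the analysis model differ in the term that matters most here. With only two surveys per practice at a fixed 12-month spacing, the change within a practice contains the intervention effect and 12 months of secular trend together. Power computed without the trend need not resemble power for the analysis that will be run. Both Aim 2 primary hypotheses rest on this paragraph.

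**Working it through.** **Inputs.** From the Aim 2 power section: β0, β3, the variance components and 200 patients per survey. The test is taken from Aim 1, where the null "is rejected with two-sided *α* = 0.05 Wald tests under the correctly specified model". Two inputs are assumptions, because the Aim 2 text does not give them: 300 practices (the recruitment target) and time in years (t = 0 and 1), so that the random slope adds σ1² to the variance of the change.

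**1. Reproducing the stated figure at 0.04.** With p0 = expit(β0):

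- Communication: p0 = 0.802, and logit(0.842) − 1.4 = 0.275.
- Shared decision-making: p0 = 0.310, and logit(0.350) + 0.8 = 0.181.

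Without a trend, Var(β3 estimate) = [σ1² + 1/(200·p0·q0) + 1/(200·p1·q1)]/300.

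- Communication: (0.32 + 0.0315 + 0.0376)/300, SE 0.0360. The ratio 0.275/0.0360 is about 7.6, so power is about 100%.
- Shared decision-making: (0.32 + 0.0234 + 0.0220)/300, SE 0.0349. The ratio 0.181/0.0349 is about 5.2, so power is 99.9%.

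The claim of more than 98% reproduces. In this model 98% power is reached at differences of about 0.022 and 0.031.

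**2. The listed effect, β3 = 0.05 (odds ratio 1.051).**

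- Communication: 0.802 to 0.810, a difference of 0.008. SE = √[(0.32 + 0.0315 + 0.0325)/300] = 0.0358. Power = Φ(0.05/0.0358 − 1.96) = 28.7%.
- Shared decision-making: 0.310 to 0.321, a difference of 0.011. SE = √[(0.32 + 0.0234 + 0.0229)/300] = 0.0349. Power = 29.9%.

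Simulating the model and fitting random intercepts and slopes gave 27% and 29%, with type I error of 5.5% and 4.0%. The β3 needed for 0.04 is 5.5 times (0.275/0.05) and 3.6 times (0.181/0.05) the listed value.

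**3. Retaining g1, taken as linear.** Let γ be the trend per month. The change within a practice has mean β3 + 12γ, so β3 = mean change − 12γ. Because every change spans 12 months, γ can be learned only from differences in level between practices with different start months. Model (3) has a readiness term, so only start months within a readiness stratum count.

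The Research design section gives 150 high-readiness practices at months 9, 11 and 12 (50 each) and 150 others at months 14 and 16 (75 each). The within-stratum sum of squares of start month is 50 × 4.667 + 150 × 1 = 383.3.

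Var(β3 estimate) = Var(change)/300 + 144 × Var(baseline level given change)/383.3.

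Communication, at a true difference of 0.04:

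- Var(change) = 0.389.
- Var(baseline) = 0.42 + 0.0315 = 0.4515.
- Covariance of baseline and change = −0.15 − 0.0315 = −0.1815.
- Var(baseline given change) = 0.4515 − 0.1815²/0.389 = 0.367.
- Var(β3 estimate) = 0.0013 + 144 × 0.367/383.3 = 0.139, so SE = 0.373.

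Shared decision-making, by the same steps: Var(change) = 0.365 and Var(baseline given change) = 0.4434 − 0.1734²/0.365 = 0.361, so SE = 0.370.

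Two-sided power for 0.04:

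- Communication: 0.275/0.373 = 0.74, power 11%.
- Shared decision-making: 0.181/0.370 = 0.49, power 8%.

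A quadratic trend gives practically the same SE, about 0.37.

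**4. Sensitivity, no trend.** With 255 practices (the 15% dropout allowed in Aim 4), power at β3 = 0.05 is 25% and 26%, and at 0.04 it stays above 99%. With t in months and σ1² = 0.32 per month², power is about 5% at β3 = 0.05 and 7 to 11% at 0.04. The stated figure therefore reproduces on a scale of years.

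**The case against.** The strongest reply is that the quoted sentence is right as it stands. It attaches more than 98% to a difference of 0.04, and that figure reproduces. No power is claimed at β3 = 0.05. Additional file 2 may tabulate several effects, and the Aim 1 text also lists β3 = 0.05 yet reports results at β3 = 0, so the value was varied there. All of this stands. A reader might infer that the power figure is an arithmetic error, or that about 29% is the true power for the planned target. The documents support neither. What remains is that the Aim 2 text calls β3 fixed at 0.05, mentions no range, and ties no β3 to 0.04.

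On g1, the omission is disclosed for Aim 2, and leaving out the trend is called a simplification in Aims 1 and 3. The planned g1 is a spline of unstated form, so a linear or quadratic trend is an assumption. That limits the precision of the 11% and 8%, but does not rescue the figure. The loss comes from the fixed 12-month spacing and the narrow range of start months, and a more flexible curve that contains the linear one cannot reduce the model-based SE.

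A reader might also hold the lack of a dropout allowance against Aim 2. The 15% belongs to Aim 4, and it does not alter the claim at 0.04 without a trend.

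**Conclusion.** The point holds in two parts. First, the listed effect and the claimed difference are not the same effect: β3 = 0.05 is 0.008 or 0.011, with about 28 to 30% power, whereas 0.04 needs β3 of about 0.275 or 0.18. This is an inconsistency in the text. Without Additional file 2 it does not show that the simulation itself was wrong. Second, the claim of more than 98% is sound only for the model without a secular trend. Under model (3) with a linear or quadratic g1, the SE of β3 is about ten times larger and power for 0.04 is about 11% and 8%.

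These figures assume 300 practices, time in years, a two-sided 0.05 test, equal allocation to the stated start months, and variance components that the article itself borrowed from Aim 1.

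**What to change.** In the Aim 2 Statistical power section:

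1. Replace β3 = 0.05 with the values that match 0.04: about 0.275 for communication and 0.18 for shared decision-making. If several values were simulated, say so and give the difference in proportions for each.
2. State the number of practices and the time unit for the random slope.
3. Label the figure above 98% as conditional on no secular trend.
4. Add the power for model (3) with g1 retained, naming the form of g1 and the start-month allocation. A figure for 255 practices can be added as a sensitivity result.

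Items 1 to 3 are edits to the text. Item 4 needs the simulation rerun with the calendar-time term in the fitted model. None of the four requires a change to the design.

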#### Aim 3: Examine the effect of primary care practice support on implementation of clinical practice and office system changes that support delivery evidence-based CVD prevention

Our primary hypothesis is that primary care practice support will increase implementation of clinical practice and office system changes to improve evidence-based CVD prevention. Our secondary hypotheses are that (a) primary care practice support intensity will increase implementation of clinical practice and office system changes, and (b) practice capacity for QI, organizational readiness to implement change, and contextual factors will moderate the effect of primary care practice support on the implementation of clinical practice and office system changes. We will explore the acceptability of primary care practice support from the perspective of the provider champion.

#### Statistical analysis

A random coefficients linear mixed model will be applied to the KDIS based on practice facilitator ratings collected monthly throughout the intervention period:4$$ E\left({Y}_{\mathrm{i}\mathrm{t}}\Big|\ {b}_{\mathrm{i}0},\ {b}_{\mathrm{i}1}\right) = {\beta}_0 + {b}_{\mathrm{i}0} + {\beta}_1{X}_{\mathrm{i}1} + {\beta}_2{X}_{\mathrm{i}2} + {\beta}_{12}{X}_{\mathrm{i}1}{X}_{\mathrm{i}2} + {g}_1\left({t}^{*};\uppsi \right) + {b}_{\mathrm{i}1}t + {g}_2\left(t;\uplambda \right)\ {X}_{\mathrm{i}\mathrm{t}3} $$where the explanatory variables and parameters are defined as in model (1). In particular, *X*_it3_ = 1 for all *t* = s_i_ + 1,…,s_i_ + 12, and *g*_2_(*t*; λ) is function for four piecewise conjoined linear segments each of 3 months duration in the intervention period with λ being the vector of slope parameters, which we expect to be positive indicating an increase in the number of clinical practice and office system changes with an increase in the amount of implementation support. The main hypothesis is an overall positive change in expected outcome between 12 months post-intervention and 1 month post-intervention. The first secondary hypothesis is that primary care practice support intensity (with *X*_it3_ re-defined and scaled as a continuous measure ranging from 0 to 1) will be positively associated with the KDIS scale *Y*_it_. The second secondary hypothesis will assess practice capacity for QI, organizational readiness to implement change, and contextual factors as effect modifiers on the rates of implementation given by *g*_2_(*t*; λ).

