### Data collection

Table 1 outlines data collection, measures, sources, and timing for each construct.

**Table 1 Tab1:** Theoretical constructs, measures, data sources, and data collection timing

Construct	Measures	Source	Timing
Implementation support	Frequency, duration, and mode of PF contacts	PF contact logs	I
	Frequency, duration, and mode of academic detailing contact	Contact, webinar logs	I
	Attendance at regional collaborative meetings	Attendance logs	I
Practice capacity for QI	Change Process Capacity Questionnaire	KI survey	B, E, F
	Adaptive Reserve Questionnaire	Provider/staff survey	B, E, F
Organizational readiness	Organizational Readiness for Change Questionnaire (ORIC)	Provider/staff survey	B
Implementation Policies and Practices (IPPs)	Key Driver Implementation Scales	PF Ratings	I
	Implementation barriers, facilitators, and IPPs	KI interview	B, E
Implementation climate	Implementation climate questionnaire	Provider/staff survey	E, F
Implementation effectiveness	ABCS measures/clinical measures	HIE	B, I, E, F
	Acceptability of implementation support	KI interview	E
Innovation effectiveness	Patient outcomes (communication, shared decision-making)	Patient survey	B, E
	Patient outcomes (healthcare utilization and mortality)	Claims data	B, E, F
	Practice outcomes (e.g., financial benefits)	KI Interview	E, F
Inner context	Practice characteristics, patient population, EMR capabilities	KI survey, PF contact logs	B, E,F
Outer context	External policies and incentives, market conditions	KI survey, KI interview, PF contact logs	B, E, F

Because readiness is conceived as an organization-level construct, we will test whether sufficient inter-rater reliability and inter-rater agreement exist to aggregate individual responses to the practice level [22–26]. If tests do not justify aggregation, we will use a measure of intra-practice variability in readiness rather than a practice-level mean in our analysis [15, 16].

Source: *PF* practice facilitator, *KI* key informant; timing: *B* baseline, *I* intervention, *E* end of intervention, *F* 6 and 12 months post-intervention

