#### Statistical analysis

The statistical analysis of the primary outcomes for Aim 1 will be based on a generalized linear mixed model (GLMM) for longitudinal binomial data at the practice level. Allowing for the number of patients who are observed within a practice to vary across time, the models will be estimated by maximizing the pseudo-likelihood, specifying practices as clusters, and using empirical variance estimators. For example, the number of hypertensive patients whose blood pressure is under control *Y*_it_, out of *N*_it_ hypertensive patients, will follow a binomial (*N*_it_, *π*_it_) distribution where, conditional upon a practice-specific random intercept *b*_i0_ and slope *b*_i1_, π_it_ = *E*(*Y*_it_/*N*_it_|*b*_i0_,*b*_i1_) is the expected proportion of hypertensive patients whose blood pressure is controlled within the *i*-th practice in the *t*-th month; *t* = s_i_ (baseline), s_i_ + 3, s_i_ + 6, s_i_ +9, s_i_ + 12, s_i_ + 18 (6 month post-intervention follow-up), and for some practices s_i_ + 24 (12 month post-intervention follow-up). The GLMM is1$$ \mathrm{Logit}\left({\uppi}_{\mathrm{i}\mathrm{t}}\right) = {\beta}_0 + {b}_{\mathrm{i}0} + {\beta}_1{X}_{\mathrm{i}1} + {\beta}_2{X}_{\mathrm{i}2} + {\beta}_{12}{X}_{\mathrm{i}1}{X}_{\mathrm{i}2} + {g}_1\left({t}^{*};\uppsi \right) + {b}_{\mathrm{i}1}t + {g}_2\left(t;\uplambda \right){X}_{\mathrm{i}\mathrm{t}3} + {g}_3\left(t;\uptheta \right){X}_{\mathrm{i}\mathrm{t}4} $$where *X*_i1_ = 1 indicates east region and 0 for west region; *X*_i2_ = 1 indicates higher readiness and 0 for lower readiness stratum; *g*_t_(*t*^*^;ψ) is a smooth spline function of calendar time (*t*^*^) for the secular trend corresponding to the control condition with finite dimensional parameter ψ; *X*_it3_ = 1 indicates the active (12 months) intervention period versus 0 otherwise and *g*_2_(*t*; λ) is function for four piecewise conjoined linear segments each of 3 months duration with λ being the vector of slope parameters; *X*_it4_ = 1 is an indicator for the maintenance period versus 0 otherwise and *g*_3_(*t*;θ) is a function for two piecewise conjoined linear segments the first of 6 months duration to which all practices will contribute data and the second 6 months durations to which only a subset of practices will contribute data as determined by the stepped-wedge design. Finally, *b*_i0_ and *b*_i1_ are assumed to be bivariately normal random variables with respective variances *σ*_0_^2^ and *σ*_1_^2^ and covariance *σ*_01_. Primary interest is in the treatment effect describing the log odds of a randomly sampled patient in a practice having the outcome 12 months post-intervention relative to the log odds of a randomly sampled patient from the same practice having the outcome during the pre-intervention period; this log odds ratio is well-defined as a function of λ parameters. Finally, the average causal effect of 12 months of intervention will be calculated as the average difference in proportions, Σ_i_[E(*Y*_it_/*N*_it_|*b*_i0_,*b*_i1_,*t* = s_i_ + 12)—E(*Y*_it_/*N*_it_|*b*_i0_,*b*_i1_*t* = s_i_)]/300; a 95 % confidence interval will be determined by bootstrapping. The random coefficients logistic model (1) will be fitted using SAS Proc GLIMMIX.

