#### Statistical power

Power is simulated using a mixed effects linear model similar to model (4) for the KDIS scale with *β*_1_ = *β*_12_ = 0 and dropping *g*_1_(*t*;ψ) giving an assumption for simplicity of no secular trend:5$$ E\left({Y}_{\mathrm{i}\mathrm{t}}\Big|\ {b}_{\mathrm{i}0},\ {b}_{\mathrm{i}1}\right) = {\beta}_0 + {b}_{\mathrm{i}0} + {\beta}_2{X}_{\mathrm{i}2} + {b}_{\mathrm{i}1}t + {\beta}_3{X}_{\mathrm{i}\mathrm{t}3} $$with *X*_it3_ = (*t*-1)/3 for *t* = 1, 2, 3, and 4. Model (5) differs from model (4) in that we model 3-month averages of KDIS scales producing quarterly data, in accordance with preliminary data reported in Figure 2 of Halladay et al., which is as follows: electronic health record (mean 2.78, sd = 3.17); care protocols (mean 1.71, sd = 4.37); planned care (mean 2.16, sd = 3.84); and self-management support (mean = 1.38, 3.67). It follows their variances are 10, 19.1, 14.7, and 13.5, respectively [15]. Model (5) assumes that the intervention effect on KDIS is linear in time during the yearlong implementation period; under this model, the main hypothesis is an overall positive change in expected outcome between 12 months post-intervention and 3 months post-intervention (*β*_3_ > 0). For power calculations, we set *β*_0_ = 2, *β*_2_ = 0.5, *β*_3_ = 1.0, *σ*_0_^2^ = 5 (or 8), *σ*_1_^2^ = 4, *σ*_01_ = −2 and *σ*_e_^2^ = 5 (or 8). Then, under the random coefficients model, Var(*Y*_it_) = *σ*_0_^2^ + *σ*_1_^2^t^2^ + 2 t *σ*_01_ + *σ*_e_^2^. Additional file 3 shows that power to show an effect of intervention on KDIS scales exceeds 85 % under the assumptions.

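### Aim 3: KDIS is never rated under control, and the main contrast does not say whether it includes the secular trend; the stated power does not apply to a trend-adjusted effect

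*Protocol article*

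**What the plan says.** - **Timing of KDIS.** Table 1 lists the "Key Driver Implementation Scales" under facilitator ratings with the intervention code only: no baseline, end-of-intervention or follow-up code. The Aim 3 analysis section describes "practice facilitator ratings collected monthly throughout the intervention period" and sets X_it3 to 1 at every reading, from month 1 to month 12 after each practice's start.
- **Model (4).** It is introduced with "where the explanatory variables and parameters are defined as in model (1", so g1(t*;ψ) keeps its Aim 1 meaning: a spline in calendar time "for the secular trend corresponding to the control condition".
- **Contrast.** The analysis section says: "The main hypothesis is an overall positive change in expected outcome between 12 months post-intervention and 1 month post-intervention". The Aim 3 power section instead takes month 12 against month 3.
- **Power.** Model (5) omits g1, "giving an assumption for simplicity of no secular trend", and power is said to exceed 85 %.
- **Claim.** The Aim 3 title and primary hypothesis speak of what practice support does to implementation, that is, of an effect.

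**The concern.** No KDIS value exists under control, so nothing observed anchors a control-condition trend. Calendar time and time on intervention can be told apart only because practices start in different months, and within a readiness stratum those months lie close together.

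The contrast can be read in two ways. Read as g2 alone, it is a trend-adjusted effect, and the power figure comes from a model without the term that makes this hard to estimate. Read as the whole change in expected outcome, it is well estimated but absorbs any calendar trend. As an illustration, a drift of 0.1 points a month over the 9 months between the first and fourth quarterly readings gives 0.9 points with no intervention effect at all, close to the 1.0 points planned for.

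On either reading the reference follows at least a month of support, so the earliest gain is left out. The two sections also differ on whether the reference is month 1 or month 3.

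**Working it through.** **Inputs from the protocol.** Research design: 150 high-readiness practices start at months 9, 11 or 12 (50 each) and 150 others at months 14 or 16 (75 each). Aim 3, Statistical power: β3 = 1.0; σ0² = σe² = 5 (or both 8); σ1² = 4; σ01 = −2; t = 1 to 4; X_it3 = (t−1)/3.

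**Assumptions.** All 300 practices contribute (Aim 3 gives no number). The test is two-sided at 5 % (stated for Aim 1). g1 takes its simplest form, γ × calendar month, with quarter t at month s_i + 3t. The random slope's time unit is varied: quarters (t = 1 to 4, as written), 0 to 1, or years.

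**Step 1: the plan's own figure, without g1.** Let h be the step per quarter in slope time (1, 1/3 or 1/4). The change D from first to fourth reading has

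Var(D) = (9h²σ1² + 9σe²/5) / 300.

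In quarters with σe² = 5: (36 + 9)/300 = 0.150, SE 0.387. On the 0 to 1 scale: (4 + 9)/300 = 0.0433, SE 0.208. In years: (2.25 + 9)/300 = 0.0375, SE 0.194. The stated figure is not reached in quarters (73 % or 68 %). It is reached on the other two scales (98 to 99.9 %).

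**Step 2: add the linear calendar term and test g2 alone.** Within a practice, calendar month and time on intervention advance together, so its readings inform only D = β3 + 9γ. The trend γ comes from comparing practices with different start months in the same stratum. The sum of squares of start months about their stratum means is

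50 × (1.667² + 0.333² + 1.333²) + 75 × (1² + 1²) = 233.3 + 150 = 383.3.

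Let V be the covariance matrix of a practice's four readings and v = 1/(1′V⁻¹1). Then Var(γ) = v/383.3. The estimates of D and γ are uncorrelated, so

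Var(β3) = Var(D) + 81v/383.3.

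Example (0 to 1 scale, variances 5): v = 5.25, so 0.0433 + 81 × 5.25/383.3 = 0.043 + 1.109 = 1.153, SE 1.07. A full GLS information matrix with region, readiness and their interaction gives the same values.

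| Slope time | σ0² = σe² | v | SE, no g1 | Power | SE, g2 alone | Ratio | Power |
|---|---|---|---|---|---|---|---|
| Quarters | 5 | 8.45 | 0.387 | 73 % | 1.39 | 3.6 | 11 % |
| Quarters | 8 | 13.57 | 0.410 | 68 % | 1.74 | 4.3 | 9 % |
| 0 to 1 | 5 | 5.25 | 0.208 | 99.8 % | 1.07 | 5.2 | 15 % |
| 0 to 1 | 8 | 9.00 | 0.248 | 98 % | 1.40 | 5.7 | 11 % |
| Years | 5 | 5.30 | 0.194 | 99.9 % | 1.08 | 5.6 | 15 % |
| Years | 8 | 9.05 | 0.236 | 99 % | 1.40 | 6.0 | 11 % |

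The effect detectable with 80 % power is 2.80 × SE, or 3.0 to 4.9 points. Table 2 runs from 0 to 5.

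**Step 3: total change with g1 kept in.** The contrast is D itself. The calendar term divides D between γ and β3 but leaves its variance alone: SE 0.387 and 0.410 in quarters, as without g1.

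**Step 4: more flexible versions.** With natural splines of 2 to 4 df, the g2-only SE in quarters rises to at most 1.50 (variances 5) or 1.85 (variances 8). On the 0 to 1 scale it barely moves (1.08, 1.41). With monthly readings and the four-segment g2, the 0 to 1 scale gives 1.20 and 1.57. Across all versions run, g2-only power is 7 to 15 %.

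**The case against.** The strongest reply is that the main hypothesis concerns change in the expected outcome, and in model (4) that expectation includes g1. On this more literal reading the contrast is total change and loses no precision. This stands: a reader might infer that following the text must destroy the power, and it need not. The g2-only reading remains open, because the same section expects positive g2 slopes and describes g2 as the rate of implementation.

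A reader might also infer that the effect cannot be estimated at all. It can: randomised staggered starts make the design matrix full rank, and the Limitations section claims only partial control of secular trends.

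Nor do the 73 % and 68 % figures show that the stated power is wrong. They depend on slope time in quarters, under which Var(Y) at t = 4 is 5 + 64 − 16 + 5 = 58, an SD of 7.6 on a 0 to 5 scale. On the 0 to 1 scale Var(Y) is 9 to 10 or 15 to 16, in line with the preliminary variances of 10 to 19.1, and power exceeds 85 %. What remains is that the time unit is ambiguous.

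Omitting g1 from the power model is openly declared, and leaving out first-month gain is conservative if that gain is positive. Neither point makes the power figure apply to a trend-adjusted effect, or turns total change into a controlled comparison.

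**Conclusion.** The point holds as a choice the plan has not made. With g1 in the model and the contrast on g2 alone, the effect is identified but imprecise: SE 1.07 to 1.74 with a linear calendar term, and 9 to 15 % power for 1.0 point under each time coding tried. With the contrast as total change, the stated power can hold, but the result is an uncontrolled within-practice change that begins after support has started. It does not support the Aim 3 wording of an effect.

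The sizes rest on 300 practices, a two-sided 5 % test, the protocol's variance components and additive g1 and g2. The number of practices for Aim 3 and the spline's degrees of freedom are not in the article, and the additional file with the power results was not available.

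**What to change.** 1. Define the primary Aim 3 contrast as total within-practice change in KDIS during the programme, and word the hypothesis and conclusion that way, without claiming an effect versus control.
2. Add one facilitator rating at kick-off (month 0), and use month 12 against month 0 as the single contrast in both the analysis and power sections.
3. Drop g1 from the primary KDIS model, or keep the g2-only estimate as a secondary analysis with its low precision stated.
4. Restate power for the model actually fitted, giving the number of practices and the time scale of the random slope.

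The cost is one extra rating per practice by facilitators who already rate monthly, and a more modest claim. A month-0 rating restores the early gain but does not create a control comparison, so item 1 is needed even with item 2.
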